##### Nurses

The first patient assessment will be discussed with a coach directly before and after completing the assessment. The second patient assessment will be performed with coaching directly afterwards. The third patient assessment will be performed without direct coaching. Diagnostic work-up and management of the first, second and third patient will be discussed with one of the coaches six weeks and three months after the nurse completed the assessment.

##### GPs

GPs will perform the assessment of the first, second and third patient on their own. Diagnostic work-up and management of the first, second and third patient will be discussed with the coach six weeks and 3 months after the GP completed the assessment.

#### Phase 2

After their participation in the workshops, and evaluation of the diagnostic work-up and management of the first three patients, GPs and nurses are expected to have been sufficiently trained to perform diagnosis and management adequately on their own. For questions during this phase, nurses and GPs will have the possibility to consult the coaches by telephone and e-mail.

#### Computerized Clinical Decision Support System (CDSS)

A CDSS is an information system designed to improve clinical decision making by using reminders [39]. Turner et al. developed and tested a CDSS especially for dementia diagnosis and management in primary care [40]. The use of this tool increased the number of dementia diagnoses reported in general practice. There was no evidence of improvement in adherence to dementia quality indicators [27]. The CCDS in the DTP has been developed for the purpose of this study. The content is based on the Dementia Guideline for Primary Care and the summarizing flow chart. It is a pro-active computer programme, which supports dementia decision making in diagnostic work-up.

### Control group

Duos in the control group will not receive the training during the trial. They will, however, be given the opportunity to attend to the DTP after the trial. This means that duos in the control group will enter the DTP with a 9 months' delay.

### Outcome measures and data collection

Primary outcome measures are the numbers of cognitive assessments and dementia diagnoses over a period of nine months, which will be measured at baseline (T0) and nine months later, at the end of the study (T1). Secondary outcomes are GPs' and nurses' attitude, confidence and knowledge regarding dementia diagnosis and management, which will be measured at baseline (T0) and nine months later, at the end of the study (T1). Other secondary outcomes are the rate of adherence to national guidelines for dementia diagnosis and management, patient satisfaction, informal carer burden and satisfaction, number of emergency calls, visits and consultations. Baseline demographic characteristics collected from GPs and nurses are: age, sex, practice experience, practice size, percentage of elderly people > 65 years and the availability of chronic disease management programs in practice. Baseline demographic characteristics collected from patients and their informal caregivers are: age, sex and co-morbidity (Table 1).

**Table 1 T1:** Outcome measures

**Variable**	**Primary outcomes**	**Secondary outcomes**	**Background**	**Instrument/Source**	**T_0_**	**T_1_**	**T_x_**

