### Bias control and randomisation

Randomisation will take place after measurement of baseline data. Duos of GPs and nurses will be randomly allocated to one of the two conditions: 1. Dementia Training Program (DTP) and 2. no training at all; control group. (Figure 1). Randomization will be concealed; a person who is not responsible for recruiting subjects and has no knowledge of the study conduct will perform it on a computer.

Cluster-randomisation will be performed in order to avoid contamination by the effects of possible exchange of information within a cluster. A cluster was defined as all GPs working in the same practice or as all GPs working together with the same nurse.

In order to assure an equal distribution of baseline characteristics, duos will be randomised with adaptive weights regarding cluster size (one vs. more than one GP), age, sex, high or low percentage of elderly patients in practice (< or > 15%), practice location (rural or urban area) and nurse affiliation (district or practice).

Adherence to guidelines will be assessed by two independent researchers. In order to exclude the possibility of detection bias, these researchers will be blinded to the outcome of randomization.

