**GPs/Nurses**							
Number of dementia diagnosis^1^		□	□	EMD^2^, self registration forms	□		□
Number of cognitive assessments^1^		□	□	EMD, self registration forms	□		□
Number of emergency consultations^1^	□		□	EMD, self registration forms	□		□
Adherence to guidelines	□		□	EMD, self registration forms/QIs	□		□
Change of knowledge	□		□	Own questionnaire			□
Change of Attitude	□		□	Own questionnaire			□
Change of skills	□		□	Own questionnaire			□
Age	□	□		Own questionnaire		□	□
Sex	□	□		Own questionnaire		□	□
Practice size	□	□		Own questionnaire		□	□
Practice experience	□	□		Own questionnaire		□	□
Percentage elderly in practice	□	□		Own questionnaire		□	□
Chronic care programs in practice	□	□		Own questionnaire		□	□

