**Informal carers**							
Age	□	□		Own questionnaire		□	□
Sex	□	□		Own questionnaire		□	□
Satisfaction intervention	□		□	Own questionnaire	□	□	
Burden informal caregiver	□		□	SSCQ^3^	□	□	

T_0 _is baseline measurement

T_1 _is follow up measurement, after 9 months

T_x _is 3 months after starting each assessment

^1 ^measurement of 'number' during a period of 9 months

^2 ^Electronic Medical Dossier

^3 ^Short Sense of Competence Questionnaire

Data on adherence to national guidelines, the number of emergency situations and the number of cognitive assessments and dementia diagnoses will be retrieved from GPs' Electronic Medical Records (EMD), from interviews with GPs and nurses and from self registration forms [41]. Self-made questionnaires will provide information on baseline characteristics, on data on GPs' and nurses' attitudes, competencies and knowledge regarding dementia diagnosis and management and on patient and informal carer satisfaction. Burden of informal carers will be assessed using the Short Sense of Competence Questionnaire (SSCQ) [42]. Data on duos' performance during the 'coaching phase' will be included in the analysis.

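### The text measures both primary counts at T0 and T1, but Table 1 appears to schedule them at T1 only, leaving the baseline count in doubt

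*Protocol article*

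**What the plan says.** Under 'Outcome measures and data collection' the article gives two time points for the primary outcomes. The first is baseline: "Primary outcome measures are the numbers of cognitive assessments and dementia diagnoses over a period of nine months, which will be measured at baseline (T0"). The second follows in the same sentence: "and nine months later, at the end of the study (T1"). The knowledge, attitude and confidence outcomes get the same two: "Secondary outcomes are GPs' and nurses' attitude, confidence and knowledge regarding dementia diagnosis and management, which will be measured at baseline (T0"), with T1 as the second.

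Table 1 lists the two primary outcomes as "Number of dementia diagnosis^1" and "Number of cognitive assessments^1", with the electronic medical record and self-registration forms as sources. Its footnote defines the counting window as "measurement of 'number' during a period of 9 months". The text below the table adds interviews with GPs and nurses as a source.

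The abstract describes the primary outcomes as counts over the nine months after the workshops and mentions no baseline count. 'Bias control and randomisation' says: "Randomisation will take place after measurement of baseline data".

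**The concern.** The article gives two schedules for its primary outcomes: T0 and T1 in the text, and one of these only in Table 1. The abstract's follow-up definition sides with the table.

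At stake is whether a count of earlier diagnosing and assessing activity exists for each duo. The variables balanced at randomisation are cluster size, age, sex, share of elderly patients, location and nurse affiliation; prior activity is not among them. With 100 duos allocated 2:1, about 33 are controls, so some chance imbalance is possible. Without a T0 count it can be neither shown nor adjusted for.

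**Working it through.** **Step 1: the marks in Table 1.** In the machine-read table each cell is either a box or blank. The rows that matter read:

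| Row | Blank under | Box under |
|---|---|---|
| Dementia diagnoses | Primary, T1 | Secondary, Background, T0, Tx |
| Cognitive assessments | Primary, T1 | Secondary, Background, T0, Tx |
| "Change of knowledge" (attitude and skills alike) | Secondary, T0, T1 | Primary, Background, Tx |
| Age (GPs and nurses) | Background, T0 | Primary, Secondary, T1, Tx |
| Carer burden | Secondary, Tx | Primary, Background, T0, T1 |

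**Step 2: decoding.** There are two possible readings.

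- *Blank means ticked, box means not ticked.* The two counts are primary. Knowledge and attitude are secondary at T0 and T1, as the text says. Age is a background variable at baseline, and carer burden is secondary. All of this fits the text.
- *Box means ticked.* The two counts become secondary and background at once, and age becomes a primary and secondary outcome. This cannot be right.

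The first reading is therefore the only coherent one. Under it the primary counts are scheduled at T1 and not at T0. The knowledge row shows that the table can express T0 plus T1, so the different pattern in the primary rows is a real difference.

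**Step 3: does any reading remove the conflict?** No. Under the second reading the primary rows would be ticked at T0 and Tx but not at T1, which also contradicts the text. Only the missing time point would change.

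**Step 4: is the sample size affected?** Inputs from 'Sample size calculations': 50% against 65%, allocation 1:2, 5 patients per cluster, ICC 0.05, power 0.80, two-sided 0.05.

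- Two proportions, pooled variance, no continuity correction: 126 control + 252 intervention = 378 patients.
- Design effect: 1 + (5 − 1) × 0.05 = 1.2, and 378 × 1.2 = 453.6.
- Clusters: 453.6 / 5 = 90.7, rounded up to 91, the stated figure.

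The calculation uses no baseline value, so 91 stands whether or not T0 is collected.

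**Step 5: what a T0 count would add.** Under linear adjustment for one baseline covariate, with correlation r between the T0 and T1 counts, the residual variance is 1 − r². The documents give no r, so a range is assumed:

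| Assumed r | 1 − r² | Variance removed |
|---|---|---|
| 0.3 | 0.91 | 9% |
| 0.5 | 0.75 | 25% |
| 0.7 | 0.51 | 49% |

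**Step 6: what a T0 count requires.** A nine-month window and a baseline that precedes randomisation mean that T0 covers nine months before allocation. No section describes registration forms being kept before enrolment. Medical records can cover that window, and interviews could do so by recall.

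**The case against.** The strongest reply is that the text commits plainly to T0 and places randomisation after baseline measurement, so Table 1 may simply carry a misprint. Nothing says that data collection follows the table in this article. The tick marks are also not visible in the machine-read copy, so the direction of the error is inferred. If T0 was not collected in time, records could still be queried later. All of this stands. It makes the consequence conditional, but the two schedules still disagree about the primary outcomes.

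A reader might infer more than the documents support:

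- **That the trial has no baseline, or that the primary comparison is invalid.** The text promises T0, and randomisation protects a T1-only comparison from systematic bias.
- **That planned power falls.** The sample size never relied on baseline adjustment; the percentages above are a gain not taken.
- **That only the medical record can supply T0.** Interviews are a listed source and can look back, though by recall.
- **That a T0-T1 change would be an artefact of changed instruments.** No section assigns different sources to the two time points. The risk arises only if forms contribute at T1 and not at T0.
- **That prior activity is known to differ widely between practices.** The documents do not quantify it.
- **That forms and interviews should be dropped from the primary count.** Nurses carry out the assessments and may be district nurses. Whether the GP record captures all their work is not stated, so a record-only count could miss some assessments.

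**Conclusion.** The point holds as a contradiction in the collection schedule of both primary outcomes. The text says T0 and T1. Table 1, on its only coherent decoding, says T1 only, and the abstract agrees with the table. The direction rests on reading blank cells as ticks and should be confirmed on the typeset table; the existence of a conflict does not depend on that reading.

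If the table is followed, baseline comparability on the primary outcomes cannot be shown and adjustment for prior activity is lost. The loss is one of precision and face validity, not of validity: 9% to 49% of outcome variance for assumed correlations of 0.3 to 0.7, with the 91 general practitioners unchanged. It should be corrected, but it does not undermine the trial.

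**What to change.** 1. Check the typeset table, then mark both T0 and T1 for the two primary rows of Table 1. Align the abstract so that it also mentions the baseline count.
2. Define T0 as a medical-record count over the nine months before randomisation, obtained in all duos before allocation.
3. Repeat the identical record query at T1 in both arms, so that a like-for-like count exists.
4. Use the T0 record count as a baseline covariate in the primary comparison.
5. Keep self-registration forms and interviews as planned sources for the T1 count. Report any T0-T1 change on the same-source record count.

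The cost is a table and abstract correction and one retrospective record query per practice. The sample size does not change.

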### Statistical analysis

In addition to a confirmatory analysis using the MANOVA-method, we will also perform an exploratory analysis. The aim of the exploratory analysis is to gain more insight into possible causal relations between the rate of success of the intervention components and the outcomes. Possible mediator variables are change in knowledge, attitudes and collaboration rate. We will design a path-model, specifying hypothesized relations between predictors, mediators, moderators, and effects, and we will test its goodness of fit with the data. In this way we hope to be able to specify the most plausible interdependence pattern between the variables used in the present study.

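### No adjustment is stated for the T0 counts, the minimisation factors or the elderly population at risk, although all are collected at baseline and adjusting for T0 is at least as precise on either reading of the MANOVA

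*Protocol article*

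**What the plan says.** **Outcomes.** Under Outcome measures and data collection: "Primary outcome measures are the numbers of cognitive assessments and dementia diagnoses over a period of nine months". The same sentence gives the timing, "which will be measured at baseline (T0) and nine months later, at the end of the study (T1"). Attitude, confidence and knowledge are also measured at T0 and T1. The baseline characteristics listed there include "practice experience, practice size, percentage of elderly people > 65 years".

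**Allocation.** Under Bias control and randomisation: "Randomisation will take place after measurement of baseline data", and "duos will be randomised with adaptive weights regarding cluster size (one vs. more than one GP), age, sex", followed by the percentage of elderly patients (cut at 15%), practice location and nurse affiliation. Practice size is not on that list.

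**Analysis.** Under Statistical analysis, the primary comparison gets one clause: "In addition to a confirmatory analysis using the MANOVA-method, we will also perform an exploratory analysis". No baseline term, balancing factor or denominator is named there, and none is excluded.

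**Scale used for planning.** Sample size calculations works with a proportion, 50% rising to 65% of the dementia population, and not with a number per duo.

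**The concern.** Three kinds of baseline information are collected and none is tied to the confirmatory comparison.

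- **T0 counts.** A practice that assessed many patients in the nine months before the trial will tend to assess many afterwards. Using the T0 count as a covariate removes that part of the variance.
- **Minimisation factors.** Balancing on prognostic factors reduces the true variance of the difference between arms. If the model leaves those factors out, its standard error does not reflect the reduction, so the test is conservative and the intervals are too wide.
- **Number at risk.** A raw number of diagnoses depends on how many elderly people the practice has. Only the percentage of elderly is balanced, in two classes. Practice size is not, so differences in size enter the outcome as extra variance.

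At stake is precision in a trial of about 100 duos. A false-positive risk is not at stake. There is also a mismatch of scale: the trial is powered on a proportion, while the outcome is defined as a number.

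**Working it through.** **1. The plan's own figure.** Inputs from Sample size calculations: 0.50 against 0.65, ratio 1:2, two-sided 0.05, power 0.80, 5 patients per cluster, ICC 0.05.
- Comparison of two proportions with pooled variance: 126 control + 252 intervention = 378 patients.
- Design effect: 1 + (5 - 1) × 0.05 = 1.2, and 378 × 1.2 = 453.6.
- 453.6 / 5 = 90.7, rounded up to 91 GPs.

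The stated 91 is reproduced. It assumes no covariate adjustment, so no stated figure is wrong.

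**2. T0: three ways to analyse the same data.** Let r be the T0-T1 correlation and assume equal variances at T0 and T1. The variance relative to T1 alone is 1 for T1 only, 2(1 - r) for a group-by-time (change) contrast, and 1 - r² with T0 as covariate. Since 1 - r² ≤ 1 and 2(1 - r) - (1 - r²) = (1 - r)² ≥ 0, the covariate analysis is never less precise than the other two, apart from degrees of freedom. The article gives no r, so the values below are assumptions. The last two columns apply 1 - r² to the calculation in step 1, as an approximation.

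| r | T1 only | change | T0 as covariate | GPs for 0.80 power | power, 100 duos |
|---|---|---|---|---|---|
| 0 | 1 | 2.00 | 1.00 | 91 | 0.84 |
| 0.2 | 1 | 1.60 | 0.96 | 88 | 0.85 |
| 0.3 | 1 | 1.40 | 0.91 | 83 | 0.87 |
| 0.5 | 1 | 1.00 | 0.75 | 69 | 0.92 |
| 0.7 | 1 | 0.60 | 0.51 | 47 | 0.98 |

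**3. What the plan's ICC implies for r and R².** On the proportion scale, the between-cluster share of the variance of a cluster mean is 5 × 0.05 / (1 + 4 × 0.05) = 0.25 / 1.2 = 0.21. Two such means from different patients, at T0 and T1, can correlate at about 0.21 at most. Factors that are constant within a cluster can explain at most about 21% of the variance. The gain from T0 is then 1 / (1 - 0.21²) = 1.045, or 1 / 0.96 = 1.042 at r = 0.2: about 4-5%.

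**4. Minimisation factors left out.** If they explain a share R² and are perfectly balanced, which is an upper bound:
- actual alpha = 2 × [1 - Φ(1.96 / √(1 - R²))];
- interval width is inflated by 1 / √(1 - R²).

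R² = 0.1 gives alpha 0.039 and intervals 5% too wide. R² = 0.2 gives 1.96 / √0.8 = 2.19, alpha about 0.03, and 1 / √0.8 = 1.12, so 12% too wide.

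**5. Number at risk.** Illustration with assumed practices: 1,500 patients with 10% elderly gives 150 people, and 3,000 with 20% gives 600, a fourfold range. Within one balanced class, 1,500 × 20% = 300 against 3,000 × 20% = 600 is still twofold. The article gives no variance of counts or of practice size, so the gain on the count scale cannot be computed.

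**6. Cost in degrees of freedom.** With 91 clusters and p covariates, the factor is about 89 / (89 - p). T0 alone costs 89/88 = 1.01, so at r = 0.2 the net factor is 0.96 × 1.01 = 0.97. T0 plus six factors, counted as one term each, costs 89/82 = 1.09. If together they explain 20%, the net is 0.80 × 1.09 = 0.87. Eight covariates cost 89/81 = 1.10, which cancels a joint correlation of 0.3 (0.91 × 1.10 = 1.00).

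**The case against.** **Silence is not exclusion.** The article gives the confirmatory analysis one clause, and a covariate list is commonly left to an analysis plan that is not shown. A reader might infer that the trial does not adjust and throws precision away. The documents support only that no adjustment is stated. This part of the objection stands.

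**T0 may already be used.** Measuring the counts at both times, and speaking of an expected change, fits a MANOVA with T0 and T1 as repeated measures. That is a fair reading, so it cannot be said that T0 is ignored. The recommendation survives it: a group-by-time contrast is at best equal to covariate adjustment, and below r = 0.5 it is less precise than ignoring T0.

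**Practice size differs by chance, not by arm.** This also stands. Unequal size is noise that a valid test allows for. A reader might infer that an imbalance in size would pass as an effect, but the documents show no mechanism for bias. The sample size section does use a denominator, so the raw-number scale is not fully settled. That is a reason to state it.

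**The gain may be small.** A reader who assumes r from 0.3 to 0.7 would claim 10% to 96% more effective duos (1 / 0.91 = 1.10; 1 / 0.51 = 1.96), and R² = 0.3 would give alpha of 0.019. The plan's ICC puts both near 0.2 on the proportion scale, so those sizes are not supported there. Degrees of freedom reduce the gain further if many covariates are weak, although close balance on the minimisation factors limits that loss.

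**Conclusion.** The point holds as a low-cost improvement, not as an error in a stated figure. The plan names a method for two counts and does not link it to baseline data that the trial collects before randomisation. On either reading of the MANOVA, T0 as covariate is at least as precise, apart from a small loss of degrees of freedom. Omitting prognostic balancing factors errs on the conservative side.

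On the proportion scale, with ICC 0.05 and 5 patients per cluster, the expected size is modest: about 4-5% from T0 if the alternative is T1 only and, at R² = 0.2, alpha of about 0.03 and intervals at most about 12% too wide. Against a change-score contrast the advantage at r = 0.2 would be larger (1.60 against 0.96). Raw counts that vary with practice size could gain more, by an amount that the article does not allow one to calculate.

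This rests on three assumptions: equal T0 and T1 variances, the plan's ICC, and T0 counts being collected as the text on outcome measures says. The tick marks in Table 1 cannot be read reliably in the extracted text, so they neither confirm nor contradict this.

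**What to change.** Specify in the analysis section that:

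1. the confirmatory comparison of the T1 counts is adjusted for the T0 count and for the minimisation factors as used in the allocation;
2. counts are taken relative to the elderly population (practice size × percentage over 65), either as an offset in a count model or as a rate in a multivariate model with covariates, with T0 on the same scale;
3. attitude, confidence and knowledge are adjusted for their T0 scores.

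Keep the covariate set to T0 and the minimisation factors, because each further term costs precision with about 100 duos. Confirm that the T0 counts are collected in every duo.

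The cost is wording and a few degrees of freedom. No new data are needed if collection follows the text, and the sample size of 91 can stay as it is. An offset would require a count model in place of MANOVA; a rate with covariates would not.
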